## Abstract

**Introduction:**

Paediatric cervical spine injury (CSI) is uncommon but can have devastating consequences. Many children, however, present to emergency departments (EDs) for the assessment of possible CSI. While imaging can be used to determine the presence of injuries, these tests are not without risks and costs, including exposure to radiation and associated life-time cancer risks. Clinical decision rules (CDRs) to guide imaging decisions exist, although two of the existing rules, the National Emergency X-Radiography Low Risk Criteria and the Canadian C-Spine Rule (CCR), focus on adults and a newly developed paediatric rule from the Pediatric Emergency Care Applied Research Network (PECARN) is yet to be externally validated. This study aims to externally validate these three CDRs in children.

**Methods and analysis:**

This is a multicentre prospective observational study of children younger than 16 years presenting with possible CSI following blunt trauma to 1 of 14 EDs across Australia, New Zealand and Singapore. Data will be collected on presenting features (history, injury mechanism, physical examination findings) and management (diagnostic imaging, admission, interventions, outcomes). The performance accuracy (sensitivity, specificity, negative and positive predictive values) of three existing CDRs in identifying children with study-defined CSIs and the specific CDR defined outcomes will be determined, along with multiple secondary outcomes including CSI epidemiology, investigations and management of possible CSI.

**Ethics and dissemination:**

Ethics approval for the study was received from the Royal Children’s Hospital Melbourne Human Research Ethics Committee in Australia (HREC/69436/RCHM-2020) with additional approvals from the New Zealand Human and Disability Ethics Committee and the SingHealth Centralised Institutional Review Board. Findings will be disseminated through peer-reviewed publications and future management guidelines.

**Trial registration number:**

Registration with the Australian New Zealand Clinical Trials Registry prior to the commencement of participant recruitment (ACTRN12621001050842). 50% of expected patients have been enrolled to date.

STRENGTHS AND LIMITATIONS OF THIS STUDYThis large cohort study will allow for external validation and possible refinement of three existing clinical decision rules on the management of possible cervical spine injuries (CSIs) in children.By using a unified study outcome, the study will allow the comparison of the performance accuracy of the three clinical decision rules.The study will describe the epidemiology and management of children with potential CSIs across multiple hospitals and countries.It is not feasible or ethical to submit all participants to an imaging test to determine the presence or absence of injury. In patients who are not imaged, medical record review and follow-up telephone calls will be used to assess outcomes.Using a prospective observational design, the study relies on clinician participation in busy clinical environments for enrolment. Furthermore, it is being conducted within tertiary paediatric and large general emergency departments which may limit its generalisability.

## Introduction

 Paediatric cervical spine injury (CSI) is uncommon, occurring in an estimated 1–2% of paediatric trauma presentations.^1^,^8^ The consequences, however, of such injuries can be devastating, resulting in spinal cord damage, long-term disability and death.^14 9^,^14^ Emergency clinicians therefore seek to identify all CSIs, often through the use of imaging including plain X-ray films (XR), CT scans and MRI.

While paediatric CSI is uncommon, assessment for *possible* CSI is not, and forms part of a standard trauma evaluation in the emergency department (ED). It is unethical and unfeasible to image all children presenting with blunt trauma for possible CSI for a number of reasons including: unnecessary exposure to ionising radiation with associated increased lifetime cancer risk, particularly with CT scans^15^,^21^; the risks of pharmacological sedation often required for young or uncooperative patients with some imaging modalities^22^,^24^; resource implications (cost, time, bed space)*;* and patient discomfort and potential harm with prolonged assessments and the use of spinal motion restriction techniques or ‘immobilisation’.^25^,^28^ Clinicians are thus faced with the decision of which children require imaging, and in whom it can be safely avoided. High imaging rates relative to the number of injuries detected have been reported from multiple countries.^5 8 29^

To address these concerns, attempts have been made to risk stratify patients with blunt trauma and identify those patients at higher risk of CSI, and thus in need of imaging, through the use of clinical decision rules (CDRs). CDRs are composed of at least three variables of patient history, physical examination findings or simple tests, and assist clinicians in making diagnostic or therapeutic decisions. CDR development is a three-step process involving derivation, validation and impact analysis (assessing the rule effect on clinician behaviour). CDRs also require validation in different population groups from which they were derived, with clinicians at different centres to ensure their wider applicability and to validate their findings,^30^,^32^ a process better known as external validation.

Until recently, there was limited paediatric-specific evidence to guide this decision-making process in the assessment of children with possible CSIs. Two high-quality and well-established CDRs, the US National Emergency X-Radiography Low Risk Criteria (NEXUS)^33 34^ and the Canadian C-Spine Rule (CCR),^35^ have been derived primarily, or entirely in adult cohorts. The features of each are detailed in table 1. Based on large prospective datasets, both CDRs are highly sensitive and efficient in reducing excess cervical spine imaging in adults. In the absence of well-validated paediatric-specific decision tools, these rules have often been used in paediatric settings, either in combination or with individual practitioner or institutional modification.^36^,^39^ The validity of their use in children, however, has been heavily questioned, particularly at younger ages.^3 40 41^ The CCR has not been validated in a paediatric cohort, and NEXUS, while reporting 100% sensitivity in their paediatric cohort, had a median paediatric age of 15 years and included only four children with CSIs younger than 9 years. Some studies applying rule criteria retrospectively have found neither performs well enough for use in children younger than 8 years.^3 40^ Two successive Cochrane reviews by Slaar *et al* and Tavender *et al*^41 42^ have identified similar issues with the application of these CDRs to paediatric populations, advising that large multicentre studies are needed to assess rule performance and projected effects on imaging rates, with particular consideration given to younger cohorts.

**Table 1 T1:** Comparison of NEXUS,^34^ CCR^35^ and PECARN^44^ criteria: study type, ages, inclusion criteria and ‘rule’ features

	NEXUS	CCR	PECARN
Study type	Prospective, observational	Prospective, observational	Prospective, observational
Age	All ages	≥16 years	<18 years
Numbers	3065 children (<18), median age 15 years34 069 patients in total (adults and children)	No children8924 enrolled	22, 430(11 857 in validation cohort, 10 572 in derivation cohort)
Inclusion criteria	Radiographic evaluationBlunt trauma	**GCS 15 and stable**Neck pain from any mechanism or, all of—visible injury above clavicles, non-ambulatory and dangerous mechanism of injury*Exclusion:* ***penetrating trauma****, known vertebral disease, acute paralysis, injury>48 hours, representation, pregnant*	Known or suspected exposure to blunt trauma with at least one of the following: evaluation by a trauma team; transported from the scene of injury to the participating hospital by emergency medical services; underwent cervical spine imaging at the participating hospital, or before transfer to the participating hospital*Exclusion: solely* ***penetrating trauma***
Rule features: history		Age>65 years	
Rule features: mechanism		Dangerous mechanism:Fall≥1 m or five stairsAxial load, for example, divingMVC>100 km/hour, rollover or ejection from vehicle; MVC involving recreational vehicleBicycle collision.	
Rule features: examination	**Altered mental status**GCS<15, disorientated, impaired memory, inappropriate response to external stimuli**IntoxicationFocal neurology**Examiner elicited or patient reported**Painful distracting injury**Any condition thought by the clinician to be producing pain sufficient to distract the patient from a CSI, for example, any long bone fracture, a significant visceral injury, a large laceration, degloving injury or crush injury, extensive burns, any other injury producing acute functional impairment**Posterior midline neck tenderness**	**GCS<15, unstable** → *exclusion criteria***Paraesthesia in extremities*Absence of low risk factor* enabling neck movement to be assessed**.*Low risk factors include:No **midline cervical spine tenderness**Delayed onset of neck painSitting position in EDSimple rear end MVCAmbulatory at any time*Inability to actively rotate neck45 degrees left and right (*providing able to be assessed—see above*)	**Altered mental status** GCS 3–8 or unresponsive on the AVPU scale (Alert, Voice, Pain, Unresponsive)***** Altered mental status: defined as GCS score of 9–14; verbal or pain on AVPU; or other signs of altered mental status. **Focal neurological deficits on examination***(includes paraesthesia, numbness or weakness)**Abnormal airway, breathing or circulation*Substantial head or torso injury**Substantial injuries were defined as those that warranted inpatient observation or surgical intervention**Self-reported neck pain or neck tenderness on examination**
Rule guidance	If no criteria present, considered at very low probability of clinically significant CSI and imaging is not required.	Provides a flow chart with specific guidance on when imaging and no imaging is indicated. Imaging is not indicated if there are no high-risk factors, a low-risk factor enabling neck movement to be assessed is present AND neck movement is assessed as normal.	If high-risk features present (*****)—consider CTIf other risk factors present on examination—consider plain X-rayIf no risk factors present—consider clinical clearance without imaging

CCR, Canadian C-Spine Rule; CSI, cervical spine injury; ED, emergency department; GCS, Glasgow Coma Scale; MVC, motor-vehicle crash; NEXUS, National Emergency X-Radiography Low Risk Criteria; PECARN, Pediatric Emergency Care Applied Research Network.

The Pediatric Emergency Care Applied Research Network (PECARN) sought to address the paucity of paediatric specific CSI CDRs, systematically developing a paediatric CSI risk assessment tool.^5 43 44^ A retrospective case control study (540 children with CSI across 17 centres) identified eight CSI-associated variables,^43^ and a subsequent prospective pilot study of 4000 children assessed the performance of the retrospective and a de novo model.^5^ Most recently, a study of 22 430 children derived and validated a CDR^44^ with a reported sensitivity of 94.3% (95% CI 90.7% to 97.9%), a specificity of 60.4% (95% CI 59.4% to 61.3%) and a negative predictive value of 99.9% (95% CI 99.8% to 100%). However, this rule is yet to be externally validated.

In addition to identifying all serious injuries, imaging-related CDRs also often aim to safely reduce the use of imaging. This is particularly important in children where ionising radiation exposure has been associated with increased lifetime cancer risk.^15^,^1719^ In an Australian single-centre study, strict application of NEXUS, CCR and retrospectively derived PECARN criteria would have increased imaging rates.^45^ This unintended consequence of the application of CDRs has been noted previously, with the desired high sensitivity often achieved at the expense of specificity.^46^,^48^ Understanding how different CDRs perform in varied clinical environments, and how they compare with current practice, highlights the importance of external validation.

NEXUS and CCR CDRs do not address the other pressing question of paediatric cervical spine imaging, namely, not only who we should image but which imaging modality should be used and when. Different imaging modalities carry different risks and costs and have different reported sensitivities in detecting CSI. Risk stratification in the PECARN rule provides such guidance with higher risk criteria triggering a CT scan and lower risk criteria triggering plain radiography of the cervical spine.^44^

The primary aim of the ‘Study of Neck Injuries in Children (SONIC)’ is to externally validate existing CDRs (PECARN, NEXUS, CCR) in an international paediatric cohort, assessing their performance accuracy and the potential impact of these rules on imaging utilisation and injury detection. This study will also enable an assessment of the epidemiology and management of possible and confirmed paediatric CSI, and missed injury rates, across study hospitals and countries. Depending on the accuracy of the validation of the existing rules, there is the possibility of refining an existing or deriving a new clinical decision rule to improve accurate detection of CSI and/or risk stratification of children with suspected CSI.

## Methods and analysis

### Design

This is a multicentre multinational prospective observational study. Study reporting will follow the Strengthening the Reporting of Observational Studies in Epidemiology,^49^ the Standards for Reporting Diagnostic Accuracy^50^ and where relevant, the Standard Protocol Items: Recommendations for Interventional Trials^51^ guidelines. This study has been registered with the Australian New Zealand Clinical Trials Registry (ACTRN12621001050842).

### Inclusion criteria

Children aged younger than 16 years with possible CSI after known or suspected blunt trauma.

Possible CSI is defined as (1) initiation of spinal precautions pre-arrival, or (2) neck pain, or (3) considered at risk of CSI by any ED assessing clinician, in the context of blunt trauma.

### Exclusion criteria

There are no specific exclusion criteria. However, patients who receive cervical spine imaging at a centre not participating in the study prior to transfer with external radiology reporting available at the time of arrival at the study ED and patients with solely penetrating trauma will be excluded from the accuracy analysis components of the study.

### Outcomes

#### Primary outcome

Performance accuracy (sensitivity, specificity, negative predictive value (NPV) and positive predictive value (PPV)) in identifying the study defined CSI (table 3) of

The PECARN risk criteria,^44^The two adult-derived CDRs (NEXUS and CCR) andCurrent CSI management practice.

**Table 3 T3:** Definitions

Study defined CSI	Cervical spine injury (CSI) is defined as vertebral fracture, ligamentous injury, intraspinal haemorrhage or spinal cord injury (SCI as diagnosed on MRI or SCI without radiological association) of the cervical region of the spine (occiput to seventh vertebra including ligamentous structures attaching seventh vertebra to first thoracic vertebra).The presence of CSI will be determined by review of the study site cervical spine imaging reports and if applicable, spine surgeon consultation notes and phone follow-up.
Imaging confirmed CSI	Formal radiology report of any trauma-related radiological cervical spine abnormality on plain radiography, CT or MRI scan.This includes vertebral fracture, facet joint subluxation or dislocation, ligamentous injury, disc injury, intraspinal haemorrhage (including subdural and extradural haemorrhage in the spinal canal) and spinal cord injury of the cervical region of the spine (occiput to seventh cervical vertebra including ligamentous structures attaching seventh vertebra to first thoracic vertebra, and C7-T1 disc).Formal imaging reports (ie, reports reviewed and finalised by fully qualified (consultant) radiologists) will be used to determine radiological diagnosis. If the diagnosis on the imaging report conflicts with the spinal surgeon consultation notes, the treating spinal surgeon will be contacted for clarification. For discrepancies between multiple imaging modalities, the interpretation of CT and MRI will supersede the interpretation of plain radiographs.
Clinically important CSI	(1) Death where CSI could be a contributing factor, (2) the need for surgical intervention for CSI, (3) any CSI-related neurological abnormality lasting>7 days or (4) imaging confirmed CSI treated with cervical spine immobilisation lasting>7 days.
Possible CSI	(1) Initiation of spinal precautions pre-arrival (2) neck pain, or (3) considered at risk of CSI by any assessing clinician, in the context of blunt trauma

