**Figure 1 F1:**
[figure not shown]
Study flow. * Verbal consent for follow up required (CRF 3). CRF, case report form; ED, emergency department.

The clinician report form (CRF 1) will be completed by the treating clinician at the time of the ED visit. Data collected will include all possible predictor variables in the PECARN risk criteria^44^ and existing adult focused CDRs^32^,^35^ prior to management decisions. Additional information to be collected is detailed in table 4. Clinical management will proceed independent of study participation.

**Table 4 T4:** Data variables to be collected

Clinical report form (CRF)	Variables collected
Clinician report form (CRF 1)	All predictor variables for CDRs under consideration.Mechanism of injury, history of injury (including symptoms and signs prehospital) and clinical ED examination.Clinician perceived CSI likelihood, neck immobilisation practice, planned imaging.
Medical record review (CRF 2)	Detailed demographics; prehospital management; management and imaging undertaken elsewhere for this injury; time-related data (times of triage, clinician evaluation, ED and hospital discharge); duration of ED and hospital stay; admission status; specialty unit consultations; use, type and duration of spinal immobilisation; analgesia; observation duration; intensive care admission, need for intubation and ventilation, duration of ventilation and duration of intensive care unit admission; specialty unit follow-up; any neck injury related representations (and imaging and interventions arranged or completed at that time); all head and neck imaging and results; CSI-related and head-injury related surgical interventions; other significant injury and mortality.
Follow-up contact (CRF 3)	CSI related symptoms (including neck pain, limb weakness/sensory changes/paraesthesias); relevant health practitioner contacts; need for and duration of ED and hospital admissions (with review of the relevant medical record); use, type and duration of spinal precautions and neurological interventions; head and cervical spine imaging modalities and results; CSI-related and head injury-related surgical interventions.
Medical record review for patients with CSI at 12 months (CRF 4)	Imaging, interventions and outcomes at 12 months in patients with confirmed CSI.

CDRs, clinical decision rules; CSI, cervical spine injury; ED, emergency department.

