#### Accuracy analysis

All patients eligible for accuracy analysis will be used to externally assess performance accuracy (sensitivity, specificity, NPV and PPV) in identifying study-defined CSI, imaging-confirmed CSI and clinically important CSI of the PECARN risk criteria,^44^ and NEXUS^34^ and CCR^35^ CDRs. When applying each CDR, items will be scored as present, absent or unknown. ‘Unknown’ predictor variables will be imputed as ‘rule negative’. The estimates of each performance accuracy measure will be reported with exact binomial 95% CIs. A sensitivity analysis will be conducted for all accuracy outcomes by using available data only, treating unknown predictor variables as missing unless one of the completed predictor variables is already rule positive. An additional sensitivity analysis for all accuracy outcomes will include transferred patients who received cervical spine imaging with radiology reports at a non-participating centre. A subgroup analysis will be conducted that restricts the accuracy analysis for patients younger than 9 years and those 9 years and older.

The accuracy of each CDR will also be calculated using the exact inclusion, exclusions, predictor and outcome variables and definitions as set out in the original publications.^34 35 44^

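### Table 3 limits the imaging source for study-defined CSI to study-site reports, so an injury documented only on an outside report can be scored negative in analyses that include children imaged elsewhere

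*Protocol article*

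**What the plan says.** Table 3 first defines study-defined CSI by type of injury and level of the spine, then names the sources from which its presence is judged: "The presence of CSI will be determined by review of the study site cervical spine imaging reports". The same sentence goes on to admit, where relevant, the spine surgeon's notes and telephone follow-up. The only imaging source named is the study site.

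The imaging-confirmed row of the same table reads "Formal radiology report of any trauma-related radiological cervical spine abnormality on plain radiography, CT or MRI scan". It requires a report finalised by a consultant radiologist but does not say at which hospital. The fourth component of clinically important CSI builds on that row: "imaging confirmed CSI treated with cervical spine immobilisation lasting>7 days".

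Three places determine where children imaged elsewhere are analysed:

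- **Exclusion criteria.** Children imaged at a non-participating centre are kept out of the accuracy analysis if they come "with external radiology reporting available at the time of arrival at the study ED".
- **Accuracy analysis.** "An additional sensitivity analysis for all accuracy outcomes will include transferred patients who received cervical spine imaging with radiology reports at a non-participating centre".
- **Analysis of non-accuracy related outcomes.** The risk of study-defined CSI is estimated in the whole study population, and the exclusion above applies only to the accuracy components.

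Table 4 shows that CRF 2 records "management and imaging undertaken elsewhere for this injury" together with all head and neck imaging results. CRF 3 records imaging modalities and results reported at follow-up.

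**The concern.** The source rule for the primary outcome is narrower than the populations to which it is applied. A transferred child may have a fracture on a CT that was done and reported at the referring hospital. If the study site neither repeats nor re-reports the imaging, that report is not among the sources listed for study-defined CSI, although it is sufficient for imaging-confirmed CSI. If the child is then immobilised for more than 7 days, the child also meets the definition of clinically important CSI. The severe subset could then contain a child whom the broad primary definition leaves out.

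Two results are at stake. The study-defined CSI rate could be too low. The transferred-patient sensitivity analysis, which should show whether leaving these children out matters, could count a true injury as a non-injury: a rule-positive child becomes a false positive, and a rule-negative child disappears as a miss. The main accuracy analysis is open to the same error for children whose outside report arrives after they do.

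**Working it through.** **Step 1: follow one child through the text.** Take a child imaged and reported as injured at a non-participating centre and not re-imaged at the study site.

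| Question | Where | Answer as written |
|---|---|---|
| Imaging-confirmed CSI? | Table 3 | Yes; any formal report counts |
| Clinically important CSI? | Table 3 | Yes if, for example, immobilised for more than 7 days |
| Study-defined CSI? | Table 3 | Only through a surgeon note or phone follow-up |
| In the main accuracy analysis? | Exclusion criteria | Only if the outside report was not available on arrival |
| In the transferred-patient sensitivity analysis? | Accuracy analysis | Yes |
| In the study-defined CSI rate? | Non-accuracy outcomes | Yes |

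The two further sources may or may not catch this child. Surgeon notes count where they exist. Follow-up contact goes to children without cervical spine imaging at the initial ED visit or later attendances. The article does not say whether imaging at the referring hospital counts as imaging for this purpose. Contact also needs verbal consent and is closed as unsuccessful after six attempts or 60 days. A loss therefore requires no re-imaging, no surgeon note and no informative follow-up, all together.

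**Step 2: the plan's own figure.** Sample size gives 100 + 50 = 150 CSIs and a CSI rate of about 0.5%. 150 / 0.005 = 30 000, which is the stated maximum enrolment. 150 / 30 000 = 0.50% (exact 95% CI 0.42% to 0.59%).

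**Step 3: possible effect on the study-defined rate.** The share of CSIs seen only on an outside report is not in the article; 5% to 30% is assumed. If no other source catches any of them:

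| Assumed share | CSIs scored | Rate = scored / 30 000 |
|---|---|---|
| 5% | 142 | 0.473% |
| 10% | 135 | 0.450% |
| 20% | 120 | 0.400% |
| 30% | 105 | 0.350% |

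If surgeon notes or follow-up catch all of them, the rate stays at 0.50%.

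**Step 4: possible effect on the sensitivity analysis.** The base is 150 CSIs and 29 850 children without CSI. Applying the PECARN sensitivity of 94.3% and specificity of 60.4% quoted in the Introduction gives 141 true positives, 9 misses and 11 821 false positives. Now add 15 or 30 outside-only CSIs (assumed), none caught by another source.

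- *Rule equally good in these children.* Counted as CSI, sensitivity is (141 + 14) / 165 = 93.9% or (141 + 28) / 180 = 93.9%. Scored as no CSI, it is 141 / 150 = 94.0%. PPV is 155 / 11 976 = 1.29% or 169 / 11 990 = 1.41% if counted, and about 1.18% if not (141 / 11 976 or 141 / 11 990).
- *Rule catches 80% of them (assumed).* Counted as CSI, sensitivity is (141 + 12) / 165 = 92.7% or (141 + 24) / 180 = 91.7%. Scored as no CSI, it is again 94.0%.

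**The case against.** The strongest case against is that nothing in the article says such a child is scored as negative. The first sentence of the definition carries no site limit. Surgeon notes and phone follow-up are admissible sources. On a plain reading, a transferred child who is not re-imaged belongs to the group contacted for follow-up, and CRF 3 records imaging results. How outside reports are adjudicated could be left to the full protocol. Children with a report in hand on arrival are not in the main accuracy analysis. The sensitivity analysis covers all accuracy outcomes, so its imaging-confirmed and clinically important versions would count these injuries properly.

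Most of this stands, and it limits the point. A reader might infer that every injury shown only on an outside report is scored as no CSI, that all CSI rates are under-counted, or that the sensitivity analysis cannot serve its purpose. The documents support none of these. Misclassification is possible only for children missed by every listed source. Only the study-defined rate is exposed. Two of the three outcome versions of the sensitivity analysis remain informative.

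What the objection does not remove is the conflict in the text. Table 3 names the study site as the imaging source in one row and sets no such limit in another, and the narrower row governs the primary outcome in analyses that deliberately admit children imaged elsewhere. That is a stated rule at odds with its use, so it is more than an omitted detail.

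**Conclusion.** The point holds as an inconsistency in the definition of the primary reference standard. Read literally, a child can be imaging-confirmed positive, and even clinically important positive, while being study-defined negative. This can touch the study-defined CSI rate, the study-defined version of the transferred-patient sensitivity analysis and, through late-arriving outside reports, the main accuracy analysis.

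The size is unknown and may be zero. The illustrative falls in the rate rest on an assumed 5% to 30% share with no capture by other sources. In the accuracy illustration, sensitivity is overstated by 1.3 points (94.0% against 92.7%) or 2.3 points (94.0% against 91.7%) only under the further assumption that the rule does worse in these children. Otherwise sensitivity hardly moves and PPV is understated by roughly 0.1 to 0.2 points. The point merits correction because it concerns the primary outcome and is easily settled; no large bias has been shown.

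**What to change.** In the study-defined CSI row of Table 3, replace the reference to study-site imaging reports with formal imaging reports from any hospital for this injury (study site, referring hospital or later hospital), as recorded on CRF 2 and CRF 3. State that the study-site report takes precedence where both read the same images. The row then agrees with the imaging-confirmed row and with the Exclusion criteria, Accuracy analysis and non-accuracy sections.

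The cost is one wording change. CRF 2 and CRF 3 already provide for outside imaging, and the Statistical methods place the analysis after all data are collected, with no interim analysis, so the change can be made before analysis. The small downside is that outside reports may vary in quality.

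### Table 3's outcome definitions do not nest: a child can have clinically important CSI in the secondary analyses and no CSI in the primary analysis

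*Protocol article*

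**What the plan says.** All the definitions stand in Table 3 of the protocol article, under Primary outcome.

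- **Study-defined CSI**, the target of the primary accuracy analysis: "Cervical spine injury (CSI) is defined as vertebral fracture, ligamentous injury, intraspinal haemorrhage or spinal cord injury", within a stated anatomical range. The list is closed.
- **Imaging-confirmed CSI**: "Formal radiology report of any trauma-related radiological cervical spine abnormality on plain radiography, CT or MRI scan". The row continues: "This includes vertebral fracture, facet joint subluxation or dislocation, ligamentous injury, disc injury, intraspinal haemorrhage", and it goes on to spinal cord injury and the C7-T1 disc. The list illustrates the opening phrase and does not limit it.
- **Clinically important CSI**, item (4): "imaging confirmed CSI treated with cervical spine immobilisation lasting>7 days". It refers to the imaging-confirmed row, not the study-defined row.
- **Check on the imaging diagnosis**: "If the diagnosis on the imaging report conflicts with the spinal surgeon consultation notes, the treating spinal surgeon will be contacted for clarification". This applies when report and notes disagree. It sets no threshold for what counts as an abnormality.

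Clinically important CSI is a secondary accuracy outcome for PECARN, NEXUS, CCR, current practice and any new SONIC rule (Secondary outcomes). Its rate is also reported (Analysis of non-accuracy related outcomes). The Accuracy analysis section adds accuracy for imaging-confirmed CSI.

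**The concern.** A reader will expect an outcome called clinically important to be the more serious part of the primary outcome. As written, item (4) can admit children whom the primary analysis counts as uninjured. Such a child, if rule-positive, is a true positive in one analysis and a false positive in the other. If rule-negative, the child is a missed injury in one and a correct clearance in the other.

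Two results are at stake. The first is the rate of clinically important CSI, which can only rise through such cases. The second is each rule's accuracy for that outcome, which would be measured partly on children outside the primary target. A difference between a rule's sensitivity for study-defined and for clinically important CSI could then reflect a different case definition, and not only greater severity.

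**Working it through.** **1. The rows side by side.**

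| Finding | Study-defined CSI | Imaging-confirmed CSI | With immobilisation >7 days: clinically important, item (4) |
|---|---|---|---|
| Vertebral fracture, ligamentous injury, intraspinal haemorrhage, cord injury | named | named | yes |
| Facet joint subluxation or dislocation | not named | named | yes |
| Disc injury, including C7-T1 | not named | named | yes |
| Any other trauma-related abnormality in a formal report | not named | admitted by the opening phrase | yes |

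The second and third lines establish the mismatch without leaning on the breadth of the opening phrase, because the article itself names these injuries in one row and not in the other. The fourth line adds a class of unstated content and size.

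**2. The plan's own event figure.** The Sample size section expects up to 30 000 patients at about 0.5% CSI: 30 000 × 0.005 = 150, which matches the target of 100 + 50. The section gives no expected number of clinically important CSIs.

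**3. Effect on sensitivity (illustration only).** Let *n* be the clinically important cases that are also study-defined, TP those that a rule detects, *m* the cases added by the wider row, and *s* the share of the added cases that are rule-positive. Then

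sensitivity = (TP + *m s*) / (*n* + *m*),

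which rises if *s* exceeds TP/*n* and falls if *s* is below it. The article gives none of *n*, *m* and *s*, so all are assumed here. The second set takes *n* = 150 from the overall CSI target and TP = 141, close to the 94.3% published for PECARN (0.943 × 150 = 141.5).

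| Core cases | Added cases | Rise in count | All added cases rule-positive | 80% rule-positive |
|---|---|---|---|---|
| 67/75 = 89.3% (80.1–95.3) | 15 | 15/75 = 20% | 82/90 = 91.1% (83.2–96.1) | 79/90 = 87.8% |
| same | 25 | 25/75 = 33% | 92/100 = 92.0% (84.8–96.5) | 87/100 = 87.0% |
| 141/150 = 94.0% (88.9–97.2) | 17 | 17/150 = 11% | 158/167 = 94.6% (90.0–97.5) | 155/167 = 92.8% |
| same | 38 | 38/150 = 25% | 179/188 = 95.2% (91.1–97.8) | 171/188 = 91.0% |
| same | 64 | 64/150 = 43% | 205/214 = 95.8% (92.2–98.1) | 192/214 = 89.7% |

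Intervals are exact binomial 95%. In the second set the added cases make up about 10%, 20% and 30% of the enlarged outcome.

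**4. Reading.** The rise in the count follows from *m* alone. The change in sensitivity takes either sign within this range, and where intervals are shown they overlap almost wholly with the core interval.

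**The case against.** **The wider phrase may be narrower in practice.** It sits in a row that defines injury, is restricted to trauma-related findings in consultant-finalised reports, and is followed only by structural, haemorrhagic and cord injuries. Soft-tissue change reported as ligamentous injury is already study-defined CSI. Minor soft-tissue or marrow change is not mentioned anywhere; its inclusion is only what a literal reading would allow. This limits the likely size of the mismatch. It does not remove it, because facet and disc injuries are named.

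**Item (4) has its own severity condition, and nothing requires nesting.** Both are true. An imaging finding alone does not qualify, and the article never says that clinically important CSI is a subset of the primary outcome. It also never says that it is not, and the label invites that assumption.

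**The separate analyses would show the difference.** Accuracy is reported for all three outcomes, and again under each rule's published definitions. Separate totals do not, however, show how many children are cases in one outcome and non-cases in another.

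**This is a condensed article.** Coding rules for borderline reports may sit in the full protocol. But the point concerns definitions that the article states, not detail that it omits.

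**A stronger reading to resist.** A reader might infer that the added cases are rule-positive almost by construction, because a collar is kept on for persisting neck pain and PECARN counts "Self-reported neck pain or neck tenderness on examination", so that sensitivity is inflated. The article does not support this. No rule in Table 1 contains immobilisation. Predictors are recorded before management decisions (Patient recruitment, study procedures and data collection), and unknown items are scored rule negative in the main analysis. The article does not say why immobilisation is continued. NEXUS needs midline tenderness or another criterion, and in CCR neck pain is a condition of entry. A high rule-positive share is plausible for PECARN, but it is not built into the definitions.

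**Conclusion.** The inconsistency is real and rests on the text of Table 3 alone: clinically important CSI is not a subset of study-defined CSI. It affects a secondary accuracy outcome for every rule assessed and the reported rate of clinically important CSI. The primary analysis is untouched.

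The count of clinically important CSI is enlarged by however many such children there are. The article does not allow that number to be estimated; the 11% to 43% in the table follows from assumed counts. Sensitivity for this outcome may move up or down by a few points, depending on a rule-positive share that is also unknown. A claim that sensitivity is inflated would go beyond the evidence. The point deserves correction because the definitions are fixed in print, feed reported results, and can be put right cheaply before analysis.

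**What to change.** Before analysis, reconcile the rows of Table 3:

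1. Replace the open-ended opening and illustrative list of imaging-confirmed CSI with a closed list.
2. State whether facet joint subluxation or dislocation and disc injury are study-defined CSI, and use the same injury list in both rows.
3. Base item (4) of clinically important CSI on that reconciled list.
4. Code other trauma-related imaging findings separately from the CRF 2 imaging results, and report how many children are cases under one definition and not under another.

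Step 2 must come before step 3. Tying item (4) to the study-defined row as now worded could drop facet and disc injuries that the article expressly lists. For the same reason, altered alignment should not be excluded as a class without first separating it from facet subluxation or dislocation.

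The cost is a change of wording and the recoding of reports that CRF 2 already collects. No interim analysis is planned, so this can be settled before any results are seen. There may be slightly fewer clinically important events, with somewhat wider intervals. If facet and disc injuries are added to study-defined CSI, the primary case count could also change, and that decision should be documented before the data are analysed.
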